### Statistical analyses

One-way analysis of variance and *χ*^2^ will be used to analyze differences in baseline characteristics and outcome measures among the three groups. Analysis of covariance will be conducted at the assessments, followed by a post hoc analysis using the Bonferroni test to identify the direction of the effects. Statistical significance will be set at 0.05 for all comparisons. We will use the “pretest” performance as a covariate to parcel out the possible confounding effects of differences in baseline performance. The group will be the independent variable and the posttest and follow-up test performance will be the dependent variable. The missing data will be adjusted based on the last observation carried forward (Herman, 2009). Partial eta squared (*η*^2^) will also be estimated to determine the group difference for each outcome measure. Predictors of intervention outcomes will be estimated with the chi-square automatic interaction detector method. Data analyses will be performed using the SPSS Statistics 18.0 software (IBM Corp, Armonk, NY).

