### Sample size estimation

No published research to date has compared the effects of bilateral RT+MT, RT+BAT, and RT+impairment-oriented training (IOT). Thus, the sample size required for this project was calculated and estimated based on our published studies [8, 21, 22].

In a previous study, we randomized 21 stroke patients to two treatments: RT+task-oriented training and RT+IOT [21]. Between-group analyses revealed small to large effects on the FMA (*p* = 0.01, *η*^2^ = 0.43), Stroke Impact Scale (*p* = 0.046, *η*^2^ = 0.29), and Medical Research Council scale (*p* = 0.98, *η*^2^ < 0.01), respectively.

An additional 21 stroke patients were randomized to receive RT+BAT or RT [8]. Between-group analyses revealed small to large effects on the FMA (*p* = 0.82, *η*^2^ = 0.003) and Goal Attainment Scale total scores (*p* > 0.01, *η*^2^ = 0.633). We randomized 23 stroke patients to two treatment groups: MT and BAT [22]. Between-group analyses revealed small to large effects on the FMA (*p* = 0.67, *η*^2^ = 0.009) and Stroke Impact Scale Version 3.0 total scores (*p* = 0.02, *η*^2^ = 0.165), respectively.

In addition, we used the pilot data of three groups for the FMA proximal UE score (*p* = 0.051, *η*^2^ = .114) to calculate sample size. In light of our previous findings [8, 21, 22], we estimate that to achieve a statistical power of 0.80 with a two-sided type I error of 0.05 and with an estimated dropout rate of 10% to 15% at the 3-month follow-up, a total sample size of 96 with 32 subjects for each group will be sufficient.

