### Design and procedure

This study is a single-blind, randomized controlled trial with pretest, posttest, and 3-month follow-up assessments. This comparative efficacy study will be based on a controlled trial with 3 arms: bilateral RT+MT, bilateral RT+BAT, and the control intervention of bilateral RT+IOT. The randomization sequence will be created by using a random number table with an allocation ratio of 1:1:1. Participants will be recruited from four study sites (i.e., National Taiwan University Hospital in Taipei, Chang Gung Memorial Hospital in Linkou, Taipei Hospital in New Taipei City, and Taipei Tzuchi Hospital in New Taipei City). Our therapists will screen eligible participants every day at each study site. When new participants are registered, a blinded research assistant will prepare a sheet containing the assigned group of the participants in a sealed envelope and give it to the therapist. A total of 96 eligible subjects will be stratified into four strata according to the side of lesion (right-side vs. left-side cerebrovascular accident) and the level of motor impairment (the cutoff will be 33 points on the FMA- UE Subscale) [23] at each of the four study sites to balance randomization assignment (4 strata with 24 subjects at each site). However, unblinding of participant’s group assignment is permissible when knowledge of the actual treatment is absolutely essential for further management of the patient.

The Ethical Committees for Human Research at the hospitals where participants are recruited have approved the study protocol. A well-trained and certified occupational therapist, who is blinded to the group assignment, study hypotheses, and intervention of the patients, will administer baseline, postintervention, and 3-month follow-up assessments. The baseline assessment will take place within 1 week before the start of the intervention, and the postintervention assessment within 1 week after the end of the intervention. Table 1 presents the timing of all study procedures.

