## Discussion

The study goal is to investigate the comparative efficacy of RT+MT, RT+BAT, and RT+IOT after stroke. The outcome measures are selected based on our previous studies [8, 10, 21, 22] and are in line with the International Classification of Function framework to facilitate interpretability of the functional significance of treatment outcomes [34]. According to our previous research [8, 10, 21, 22], hybrid bilateral therapy (RT+MT and RT+BAT) may result in greater recovery of the primary outcome (i.e., FMA) compared with the control condition (RT+IOT). The RT+MT group may improve sensory function more than the RT+BAT and the control groups. In addition, the combined use of subjective and objective assessments would provide more comprehensive information regarding participants’ actual and perceived improvements.

Our hybrid regimens are unique in using bilateral robotic practice as a priming technique to augment bilateral task practice with and without mirror visual feedback. The anticipated benefits of robot-assisted bilateral movement priming in stroke rehabilitation may be associated with balanced excitability between the ipsilesional and contralesional hemispheres [35], positive reorganization in the motor cortex [36, 37], and improvements in later voluntary and complicated task performance [38]. The context-related and goal-directed practice in our treatment protocol may assist the patients to transfer therapeutic gains in clinics to their real-life environment and generalize motor improvements to performance of daily activities [21].

Mirror visual feedback of the unaffected UE is provided when both UEs perform bilateral tasks in the RT+MT group, which is expected to have more improvements in sensory function over the other two groups. It is possible that the illusory visual feedback to be substituted for inadequate proprioceptive input of the affected UE may activate multimodal neurons in parietal cortex [39]. This activation may contribute to improvements in somatosensory deficits [40, 41], which are frequent in patients recovering from stroke [42]. Given the promise of improving sensorimotor outcomes using mirror visual feedback during bilateral task practice, our research will study the therapeutic benefit of RT hybridized with MT relative to the dose-matched comparison treatment.

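### The planned 0.80 power reproduces only for the three-group omnibus test; the hybrid-versus-control comparisons on the FMA, tested with Bonferroni, have about 0.64 to 0.73 each if both hybrids work equally well

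*Protocol article*

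**What the plan says.** Three parts of the protocol article bear on this.

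- **Sample size estimation.** The total is set "to achieve a statistical power of 0.80 with a two-sided type I error of 0.05". Allowing for 10% to 15% loss by three months, the section concludes that "a total sample size of 96 with 32 subjects for each group will be sufficient". It reports results of three two-group studies and then adds that "we used the pilot data of three groups for the FMA proximal UE score" (eta-squared .114). It does not name the test that has 0.80 power, and it mentions neither pairwise comparisons nor an adjustment for them.
- **Statistical analyses.** ANCOVA with group as factor and pretest as covariate is applied to posttest and follow-up, "followed by a post hoc analysis using the Bonferroni test to identify the direction of the effects". The significance level is 0.05, and missing values are filled by last observation carried forward (LOCF).
- **Discussion.** The expectation on the primary outcome is that "hybrid bilateral therapy (RT+MT and RT+BAT) may result in greater recovery of the primary outcome (i.e., FMA) compared with the control condition (RT+IOT". This is a directional comparison of each hybrid with control.

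**The concern.** An omnibus F test can say that the three arms are not all equal. It cannot say that RT+MT or RT+BAT is better than RT+IOT. Under this plan those statements come only from the post hoc step, where each of three pairs is tested at 0.05/3 = 0.0167. If the sample size was set for the omnibus test, the stated 0.80 does not describe the comparisons on which the trial will be read. One of two real benefits could then be missed more often than the power statement suggests.

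A second issue is efficiency. With exactly three arms, a significant omnibus test already provides the protection needed to test the pairs at 0.05, so the Bonferroni division spends power without need.

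**Working it through.** **Inputs from the protocol.** Two-sided alpha 0.05; power 0.80; eta-squared .114; dropout 10% to 15%; 96 patients, 32 per arm, allocated 1:1:1; ANCOVA followed by Bonferroni over three pairs; LOCF for missing data.

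**Assumptions added here.** Eta-squared .114, a pilot value for the proximal score, is taken as the ANCOVA-scale effect and applied to the FMA-UE total. The main scenario follows the Discussion: both hybrids better than control by the same amount.

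**Step 1: reproduce the 0.80.** f² = 0.114/(1 − 0.114) = 0.114/0.886 = 0.1287, so f = 0.359. The noncentrality is λ = f² × N, with 2 and N − 3 degrees of freedom (N − 4 with the covariate makes no material difference).

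- N = 78: λ = 0.1287 × 78 = 10.04, power 0.800. This is the smallest N that reaches 0.80.
- Inflation for 15% dropout: 78/0.85 = 91.8, so 92, or 93 in equal arms. The next multiple of 12 (three arms, four sites) is 96. That last rounding is a guess, because the protocol does not show its route.
- 96 × 0.85 = 81.6, about 27 per arm. At N = 81, λ = 10.42 and power is 0.816.

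The stated figure is therefore consistent with the omnibus test.

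**Step 2: the implied pairwise difference.** For standardised means (d, d, 0), f = d × √(2/9). So d = 0.359/0.471 = 0.761 SD for each hybrid against control.

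**Step 3: power of the pairwise tests.** With n per arm, the pairwise t statistic has noncentrality d × √(n/2). At n = 27 this is 0.761 × √13.5 = 2.80. The two-sided critical value at 0.05/3 with 77 degrees of freedom is 2.447, against 1.991 at 0.05. The joint events were simulated: omnibus F at 0.05, then pairs at 0.05/3 (as planned) or at 0.05 (closed test).

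| Analysed per arm | Omnibus | Bonferroni: per pair | at least one | both | Closed test: per pair | both |
|---|---|---|---|---|---|---|
| 27 (15% lost) | 0.816 | 0.635 | 0.787 | 0.484 | 0.741 | 0.666 |
| 29 (10% lost) | 0.846 | 0.674 | 0.819 | 0.530 | 0.776 | 0.707 |
| 32 (LOCF keeps all) | 0.882 | 0.726 | 0.859 | 0.593 | 0.821 | 0.759 |

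Under Bonferroni, about 38 analysed per arm would be needed for 0.80 per pair.

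**Step 4: where the loss arises.** At 27 per arm, Bonferroni without a preceding omnibus test gives 0.636 per pair, and with it 0.635. Requiring the omnibus test first costs almost nothing. The loss comes from testing at 0.05/3.

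**Step 5: sensitivity to the pattern of means.** With evenly spaced means at the same eta-squared, f = d × √(1/6), so the extreme pair differs by 0.879 SD and each adjacent pair by 0.439 SD. At 27 per arm, planned power is 0.777 for the extreme pair and 0.209 for each adjacent pair.

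**Step 6: error control of the closed test.** With three arms, if exactly one pair is truly equal, the only intersection hypothesis above it is global equality, which the omnibus test covers at 0.05. Simulated family-wise error at 27 per arm was 0.049 to 0.051, both under the global null and with one arm apart. The planned procedure runs at 0.042 and 0.017 respectively. The closed test also rejects every pair that the planned procedure rejects.

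**The case against.** Bonferroni after ANCOVA is standard, controls the family-wise error and comes with matching simultaneous intervals, which the closed test lacks. That stands: this is a matter of efficiency and of an inapplicable power statement, not of invalid inference.

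The Sample size estimation section names no test and also cites two-group studies, so the omnibus reading of the 0.80 is an inference. That stands too, although the three-group effect reproduces the figure and nothing in the section points to pairwise tests.

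Several stronger readings are tempting but not supported:

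- **That the trial simply has 0.64 power.** This is one scenario: equal hybrids, 15% lost and not analysed, and the proximal-score effect carried over to the total. The dropout figure refers to the 3-month follow-up, and LOCF may keep up to 32 per arm, which gives 0.73.
- **That the plan corrects twice.** Step 4 shows that the preceding omnibus test costs almost nothing.
- **That a significant omnibus test would often end with nothing declared.** With equal hybrids and 27 per arm, at least one hybrid is declared better than control with power 0.787, against 0.816 for the omnibus test, a gap of about 3 points. The material loss is for a given pair and for both together, and the protocol does not make showing both a criterion of success.
- **That the closed test restores 0.80.** It does so at 32 per arm (0.82) but not at 27 (0.74).

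A fair caution remains. The plan tests many outcomes at two time points and foresees interim analyses. The 5% control of the closed test holds only within one outcome and time point.

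**Conclusion.** The concern holds in a limited form. On the only three-group effect given, the 0.80 is reproduced as omnibus power and does not carry over to the comparison of each hybrid with RT+IOT. With equally effective hybrids (d about 0.76), the planned Bonferroni step gives roughly 0.64 to 0.73 per comparison and 0.48 to 0.59 for both. Changing only the pairwise level to 0.05 after a significant omnibus test gives 0.74 to 0.82 per comparison and 0.67 to 0.76 for both. That is about 10 points per pair and 17 to 18 points for both, with no added patients.

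These figures rest on eta-squared .114 applying to the FMA-UE total, on the two hybrids being equal, and on 27 to 32 analysed per arm. Unequal hybrids change the per-pair figures considerably, as the evenly spaced case shows. The change is a worthwhile and cheap improvement; the planned test is not an error.

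**What to change.** In Statistical analyses, replace the Bonferroni step as follows: for each outcome and time point, test the omnibus ANCOVA at 0.05 and, if it is significant, test each of the three pairwise adjusted differences at 0.05. State that this is a closed test for three arms, with family-wise control at 5% within that outcome and time point.

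In Sample size estimation, say that 0.80 refers to the omnibus test, if that is what was calculated. Add the power of the hybrid-versus-control comparisons as a range, with its assumptions: effect size and its source in the proximal score, pattern of means, and number analysed per arm.

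The cost is wording only. There are two downsides to accept openly. The closed test has no matching simultaneous confidence intervals, and it does nothing about multiplicity across outcomes, time points or interim looks. If simultaneous intervals matter more to the investigators than power, Bonferroni can stay, but the power statement should still be restated for it.

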### Outcome measures

#### Primary outcome measurement

##### Fugl-Meyer Assessment (FMA)

The UE subscale of the FMA will be used to assess motor impairment [18]. There are 33 UE items measuring the movements and reflexes of the shoulder/elbow/forearm, wrist, hand, and coordination/speed. Each score is on a 3-point ordinal scale (0 = cannot perform, 1 = performs partially, 2 = performs fully), with a maximum score of 66 as optimal recovery. The subscale score of a proximal shoulder/elbow (FMA s/e: 0–42) and a distal hand/wrist (FMA h/w: 0–24) will be calculated to investigate the treatment effects on separate UE elements. The FMA has good reliability, validity, and responsiveness in stroke patients [26].

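### No single FMA score and time point is fixed as primary, so the 5% error rate used to size the trial is not secured for the primary claim

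*Protocol article*

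**What the plan says.** The Primary outcome measurement section of the protocol article names the FMA upper-extremity subscale (maximum 66). It adds that a proximal score (0-42) and a distal score (0-24) "will be calculated to investigate the treatment effects on separate UE elements".

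Under Statistical analyses, group is the independent variable, the pretest is the covariate, and "the posttest and follow-up test performance will be the dependent variable". The significance rule is "Statistical significance will be set at 0.05 for all comparisons". The Bonferroni step is described only as a post hoc procedure after the ANCOVA, to locate differences among the groups.

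Under Sample size estimation, "we used the pilot data of three groups for the FMA proximal UE score" (eta squared 0.114) describes the effect used for the calculation. The target is a "statistical power of 0.80 with a two-sided type I error of 0.05", with an "estimated dropout rate of 10% to 15% at the 3-month follow-up", and the conclusion is that "a total sample size of 96 with 32 subjects for each group will be sufficient".

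The Discussion states the efficacy hypothesis on the FMA, without naming a score or a time point.

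**The concern.** The sections do not point to one endpoint. The outcome section leads with the total, the sample size uses the proximal score, the dropout allowance refers to the 3-month visit, and the analysis section treats posttest and follow-up alike. Three scores at two times give six omnibus tests under the primary heading, each at 0.05. The only stated multiplicity step works within a test, among arms, and not across the six.

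The stake is the primary claim. If the result to be presented as primary can be chosen after the data are seen, the single two-sided 0.05 used to size the trial no longer describes the risk of a false claim. The Trial status section says recruitment was under way at submission, and the Data management and quality section plans interim analyses. The choice should therefore be made before any group comparison is available.

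**Working it through.** **1. The plan's own sample size.**

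Inputs from Sample size estimation: eta squared 0.114, power 0.80, two-sided 0.05, dropout 10-15%, N = 96. Three arms at 1:1:1 come from Design and procedure; one covariate comes from Statistical analyses.

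- Effect size: f = sqrt(0.114 / (1 - 0.114)) = sqrt(0.114 / 0.886) = 0.359.
- Power is from the noncentral F with 2 and N - 4 degrees of freedom and noncentrality N × f². The smallest N with power 0.80 is 78 evaluable.
- With dropout: 78 / 0.90 = 86.7, so 87; 78 / 0.85 = 91.8, so 92 (93 if balanced).
- In the other direction: 96 × 0.85 = 81.6 evaluable, power 0.82.
- With f rounded to 0.35, 82 are needed (84 balanced, 28 per arm); 28 / 0.90 = 31.1, so 32 per arm and 96 in total.

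The planned 96 is consistent with one omnibus test of the proximal score at 0.05. It contains no allowance for several tests.

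**2. False-positive risk across scores and times.**

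The protocol gives no correlation between proximal and distal scores or between time points, so these are assumptions. Simulation under no group difference: 32 per arm, omnibus F at 0.05, baseline-adjusted residuals, total = proximal + distal, proximal-to-distal SD ratio 1.5, 20,000 runs per setting. The proximal-distal correlation was varied from 0 to 0.8 and the between-time correlation from 0.5 to 0.9.

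| What would count as a positive primary result | Chance of at least one false positive |
|---|---|
| One score at one time | 4.7-5.3% |
| Total score, either time | 7.0-9.4% |
| Any of three scores, one time | 7.9-12.0% |
| Any of three scores, either time (six tests) | 11.7-20.6% |

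- Narrower assumptions for the six tests (proximal-distal 0.3-0.7, between-time 0.6-0.8) give 13.7-18.4%.
- With 15% of follow-up values carried forward and a between-time correlation of 0.7, the six-test figure is 16.1% (proximal-distal 0.5) or 17.7% (0.3).
- Independence bounds: two tests, 1 - 0.95² = 9.75%; six tests, 1 - 0.95⁶ = 26.5%. The six-test bound cannot be reached, because the total is the sum of the other two scores.
- The planned interim analyses are not included in any of these figures.

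**3. Splitting alpha instead of naming one endpoint.**

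- Two times at 0.025 each: 94 evaluable needed; power about 0.74 with 82 evaluable.
- Six tests at 0.05 / 6 = 0.0083 each: 117 evaluable needed; power about 0.59 with 82 evaluable.

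One named endpoint at 0.05 needs 78, so it is the option that the planned 96 supports.

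**The case against.** A reader might infer that the plan declares three co-primary scores at two times, with success on any one of six, and so carries a false-positive rate of some 14-18%. The document does not support that. It names one primary instrument. Its wording on the proximal and distal scores also fits a descriptive breakdown of the total. It states no any-of-six rule and gives no correlations. The 14-18% belongs to one subset of assumed correlations, and the 26.5% for independent tests cannot apply here.

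The follow-up also has a purpose of its own. The Background says that retention and possible delayed response will be examined there, so it is not simply a second attempt at the same claim. This is not a ranking, however. A delayed response could itself be presented as an effect, and the analysis section does not order the two times.

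The secondary instruments are tested under the same 0.05 rule, but that does not raise the error rate of the primary claim. Barring all significance tests on them would be a matter of preference.

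Finally, only a condensed article is shown, and an ordering of tests is often left to an analysis plan. Silence alone would not be a finding. Here, though, the article does state a rule, 0.05 for every comparison with Bonferroni only among arms, and it sizes the trial on a different score from the one that leads its primary outcome section.

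**Conclusion.** The concern holds in this form: no one FMA score and time point is fixed to carry the primary claim, and the stated testing rule does not hold the error at the 5% assumed in the sample size. The inflation depends on what would be accepted as a positive result. It is about 7-9% if the total at either time counts, and about 12-21% if any of the six tests counts. Both ranges rest on assumed correlations and an assumed SD ratio. Neither is a declared property of the plan, because the document does not say what counts as success. The 5% holds only for one score at one time, which the document does not specify. The planned 96 is adequate for that single test if the proximal pilot effect applies to the score chosen.

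**What to change.** Before any interim or final group results are seen:

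- Name one primary endpoint, for example the FMA upper-extremity total at posttest, with the three-arm ANCOVA tested at 0.05.
- Test the same score at 3 months at 0.05 only if the first test is significant (fixed sequence). This keeps the full 0.05 for the first test and needs no extra participants.
- Label the proximal and distal scores and the secondary instruments as supportive or exploratory.
- Restate the sample-size basis for the chosen score. If eta squared 0.114 also holds for it, 78 evaluable are needed and 96 is adequate. If the total is chosen, say why the proximal effect is taken to apply. The other FMA effects cited in that section come from two-arm studies and range from 0.003 to 0.43, so they do not settle the matter.

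The cost is a few sentences in the outcome, analysis and sample-size sections. The downside is that fewer results can be called confirmatory, and a difference seen only at 3 months could not be claimed as one.

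### Randomisation is stratified by lesion side and FMA-UE level within four sites, but the ANCOVA contains only group and the outcome's own pretest

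*Protocol article*

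**What the plan says.** Under Design and procedure, the article says that the 96 participants will be "stratified into four strata according to the side of lesion (right-side vs. left-side cerebrovascular accident) and the level of motor impairment", where "the cutoff will be 33 points on the FMA- UE Subscale". This is done "at each of the four study sites to balance randomization assignment (4 strata with 24 subjects at each site"). Two sides by two severity levels by four sites gives 16 cells, averaging 96/16 = 6 patients. On the sequence itself it says: "The randomization sequence will be created by using a random number table with an allocation ratio of 1:1:1".

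Under Statistical analyses, the model is an ANCOVA. "The group will be the independent variable and the posttest and follow-up test performance will be the dependent variable". The only covariate named is pretest "performance as a covariate to parcel out the possible confounding effects of differences in baseline performance". The level is fixed as well: "Statistical significance will be set at 0.05 for all comparisons". No section says that the analysis takes account of site, lesion side or the severity stratum.

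The primary outcome is the FMA upper-extremity subscale. The secondary outcomes include the Stroke Impact Scale, Medical Research Council scale, Revised Nottingham Sensory Assessment, ABILHAND, Goal Attainment Scale, Functional Independence Measure, Stroke Self-Efficacy Questionnaire and accelerometer counts.

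**The concern.** The design treats site, lesion side and motor severity as important enough to control at assignment, and the analysis then drops them. An article may leave details to a fuller plan. This one, however, fixes the dependent variable, factor, covariate, post hoc test and missing-data rule, so the point is about a model as stated.

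What is at stake depends on how assignment works within the cells:

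- **Balanced within cells.** The group estimates already benefit from the balance. The variance that the strata explain nevertheless stays in the residual, so the reported standard errors overstate the real uncertainty. Confidence intervals are too wide, the tests reject too rarely and power is lost.
- **Not balanced within cells.** The standard errors are valid for the model fitted. The estimates are less precise than they could be, and chance differences between arms in site or side stay unadjusted.

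For the primary FMA outcome, the continuous pretest FMA already carries most of the severity stratum, so the omission is mainly of site and side. For every other outcome the pretest is that outcome's own score, and all three design factors are left out.

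**Working it through.** **Inputs from the article.** N = 96 in three arms; 80% power; two-sided alpha 0.05; dropout 10% to 15%; pilot η² = 0.114 for the proximal FMA score (Sample size estimation). Four sites, two sides and two severity levels (Design and procedure).

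**Input assumed.** R2 is the share of the variance left after the pretest that the omitted factors explain. The article gives no value. I use 0 to 0.15, including 0 because the strata may add nothing beyond the pretest.

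**1. The article's own sample size.** f² = η²/(1 − η²) = 0.114/0.886 = 0.1287, so f = 0.359. The noncentral F test with 2 numerator df and noncentrality N × f² needs 78 completers for 80% power. Inflated for dropout, this is 78/0.90 = 87 or 78/0.85 = 92 (93 for equal arms). The stated 96 is slightly above this and covers it. At 15% dropout, 96 × 0.85 = 81.6, or about 82 completers. With the pretest as covariate the residual df are 82 − 3 − 1 = 78 and power is 0.821.

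**2. Standard errors, patients and actual alpha.**

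- Ratio of pretest-only to adjusted standard error: 1/√(1 − R2)
- Patients effectively given up: 96 × R2
- Actual alpha of a nominal 5% comparison under within-stratum balance: 2 × [1 − Φ(1.96/√(1 − R2))]

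| R2 (assumed) | SE ratio | Patients of 96 | Actual alpha if balanced |
|---|---|---|---|
| 0 | 1.000 | 0 | 0.050 |
| 0.02 | 1.010 | 1.9 | 0.048 |
| 0.05 | 1.026 | 4.8 | 0.044 |
| 0.10 | 1.054 | 9.6 | 0.039 |
| 0.15 | 1.085 | 14.4 | 0.034 |

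The last column applies only if assignment is balanced within strata. Without such balance, alpha stays at 0.05.

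**3. Power after adding the factors.** Noncentrality becomes 82 × f²/(1 − R2). The residual df become 74 with site (3) and side (1), or 73 with one further severity term.

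| R2 (assumed) | Pretest only | With factors, 74 df | With factors, 73 df |
|---|---|---|---|
| 0 | 0.821 | 0.821 | 0.820 |
| 0.05 | 0.821 | 0.841 | 0.841 |
| 0.10 | 0.821 | 0.861 | 0.861 |
| 0.15 | 0.821 | 0.881 | 0.881 |

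This takes η² = 0.114 as the effect in the pretest-only model. If the strata explain nothing, the extra df cost about 0.1 percentage point of power.

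**4. Simulation check.** The setting was 96 patients, four sites of 24, assignment blocked within cells, and f about 0.36, with 3,000 null and 1,500 alternative runs.

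- R2 about 0.05: mean SE 0.255 pretest-only against 0.251 adjusted; power 0.863 against 0.871.
- R2 about 0.12: type I error 0.039 against 0.050; power 0.853 against 0.877.
- R2 about 0.24, beyond the assumed range and shown for the mechanism: the true SD of the estimate was 0.260 pretest-only and 0.258 adjusted, so the estimates were equally precise. The mean reported SE was 0.280 against 0.252, and type I error 0.029 against 0.049.
- R2 = 0: no meaningful difference.

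The simulation confirms the direction. Under balance, the fault lies in the reported standard error and not in the estimate.

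**The case against.** The strongest reply is that the harm is mild and its size unknown. The estimate is unbiased and the test errs on the safe side. Pretest-only power with 82 completers is 0.821, already above the planned 0.80. The primary outcome is the FMA, whose pretest absorbs most of the severity stratum. R2 is not documented, and at 0.02 the standard error is only 1% too wide. All of this stands. It limits the size of the point but does not remove it, because adjustment costs almost nothing even when R2 is 0.

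Three stronger readings are tempting, and the document supports none of them.

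- **That the sequence cannot balance the cells.** A reader might take "random number table with an allocation ratio of 1:1:1" to mean simple randomisation and compute how often arms or cells come out unequal. A random number table is a source of randomness and does not exclude blocks. The same section gives an equal ratio, strata within site and balance as the purpose, and an article commonly leaves the blocking method to the full protocol. Such probabilities would describe a design that the article does not state, and they could not hold together with the conservative alpha in the table, which needs balance. There is no basis here for asking for new assignment lists.
- **That false positives rise or the estimates are biased.** Neither follows, whether or not assignment is balanced within cells.
- **That up to 17 patients are lost.** 96/0.85 − 96 = 16.9 is the additional enrolment that would offset the loss at R2 = 0.15. The number effectively given up out of 96 is 96 × 0.15 = 14.4.

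**Conclusion.** The mismatch between design and model is real, and the remedy is close to free. Site and lesion side are in no model, and motor severity is missing for all non-FMA outcomes. Over an assumed R2 of 0 to 0.15, pretest-only standard errors are 0 to 8% wider, worth 0 to about 14 of 96 patients. Power with 82 completers would rise from about 0.82 to between 0.82 and 0.88. If assignment is balanced within strata, the nominal 5% test runs at 0.050 to 0.034. If it is not, alpha is correct, and the cost is lost precision plus unadjusted chance imbalance.

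These figures rest on the assumed R2, on the article's pilot η² and on 15% dropout. For the primary FMA the relevant R2 is that of site and side only, so the lower part of the range is the more plausible there. The planned sample size remains sufficient either way. This is an improvement that should be made and not a threat to the validity of the trial.

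**What to change.** Add one sentence to Statistical analyses: every ANCOVA will include group, the outcome's own pretest, site (3 df) and side of lesion (1 df) as fixed main effects, and for outcomes other than the FMA also the baseline FMA-UE score as a continuous covariate (1 df). Main effects are preferable to crossing the factors, because the 16 cells average only 6 patients.

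The cost is 4 to 5 df of about 80, or about 0.1 percentage point of power if the factors turn out to explain nothing. All the variables are already collected for stratification, and the sample size does not change. Trial status reports that recruitment was continuing at submission, so the sentence should be fixed before any analysis by group is seen, including the interim analyses mentioned under Data management and quality.
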